## Discussion

With the number of older people strongly increasing in almost all countries, frailty prevalence is expected to rise dramatically [2], placing a heavy burden on health and aged care systems [88, 89]. As clinical studies in frail older patients are challenging and still rare, or yielded inconsistent results, procedures to reliably identify early onset stages of frailty as well as appropriate interventions to prevent disability and preserve physical functions are desperately needed.

The objective of our intervention is to increase relevant input into the sensorimotor system in order to engage competitive processes in the brain that refine the representations of sensory inputs and motor actions, thereby increasing the strength of cortical resources and reversing the maladaptive “disuse” of the brain [5]. Therefore, we expect our approach to promote sensorimotor and physical abilities, including motor stability, gait, and extremity function, and to reduce maladaptive behaviors, such as inactivity and social isolation, thereby leading to an improvement in frailty status.

Previous interventional studies in frailty included various types of intervention, such as physical exercise [24, 90, 91], nutritional intervention [92, 93], cognitive training [94], or geriatric assessment intervention [95, 96]. In particular physical exercise interventions demonstrated to be effective in reducing frailty and improving physical performance, while other interventions revealed only small or no training effects [25, 29]. This heterogeneity of study results might be due to differences in the study protocols with respect to training protocol, intensity, frequency, delivering method, and outcome measures. Thus, the reasons why some interventions are effective while others are not still remain unclear. This impedes interpretability and generalizability of the findings [29].

Despite the fact that frailty is associated with a decline in multiple physiological systems [1], the role of the central nervous system and in particular the brain in the pathogenesis of frailty has been addressed in only a small number of studies and still remains unclear. In fact, evidence suggested a link between frailty and brain physiology. For instance, the physical frailty phenotype has been related to reduced cerebellar gray matter volume [97], and some of the phenotype criteria, particularly walking speed, have been associated to regional brain volumes in the prefrontal cortex [6] and corpus callosum [98]. Moreover, evidence suggested a clear link between frailty and cognition, such that the presence of frailty can predict cognitive impairment and neurodegenerative diseases, such as dementia, within a few years [99, 100]. In this context, neurotrophic factors, including BDNF, may play an important role in survival, due to their role in promoting the differentiation of new neurons and synapses [101] and in preventing neuronal death during stress [102]. In fact, physical therapy intervention was found to increase plasma BDNF levels in pre-frail elderly women, suggesting that BDNF may be a key mediator in the pathophysiology of frailty [28]. However, interventional studies in frailty focusing on training effects in the brain are still lacking.

With the current trial, we will employ a multidimensional characterization of frailty, including neurophysiological, physical, sensorimotor, cognitive, and functional variables, which will enable us to investigate training effects on frailty status as well as on frailty-related outcomes. Through our intervention, we will target core central nervous processing in the sensorimotor system, by which we intend to create a link between structural, functional and biological markers of neuroplasticity and potential changes in frailty status. This approach aims at identifying the underlying pathogenic mechanisms of frailty and the results may add to previous interventional studies by offering new possible explanations for training effects found in frailty status and peripheral physical outcomes, such as muscle strength and muscle mass. Moreover, our study will provide new insights into how to prevent the continuous decline and avoid adverse outcomes in the development of frailty. This is important because frailty is a condition, which evolves from a subclinical state into a state of decompensation and ultimately overt frailty in the presence of stressors [103, 104]. Depending on one’s preceding frailty state, transitions between frailty states may occur frequently over time and may also be recurrent, suggesting that frailty is a dynamic process [41]. By including frail as well as pre-frail subjects, we will be able to relate the training effects to changes in frailty status across a broad range of severity levels of pathological aging. In this context, our study might contribute to identify useful strategies, such as the maintenance of sensorimotor stimulation and function, for slowing progression in an early state and preserving older people’s physical functions, autonomy, and quality of life that future studies can be based on.

### Strengths and limitations

The present study has several strengths. First, the study includes an innovative multimodal sensorimotor approach designed to specifically target mechanisms of pathological neuroplasticity in frailty, compared to an active control condition. Second, participants will be recruited from the general population instead of clinical institutions. This will increase generalizability of the results and approach. Third, the treatment procedures are conceptualized as home-based training, thereby presumably increasing compliance for daily care.

The study is also subject to some limitations. Researchers and participants will not be blinded to treatment condition. However, by randomly assigning subjects to the treatment conditions and by using an appropriate active control group, we aim to eliminate any effects of expectations or systematic biases from inducing performance differences. The study design does not include follow-up assessments going beyond post-training measurements after completion of the training, which should be addressed in future studies.

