### Randomization and blinding

Subjects will be randomly allocated on a 1:1 ratio to either the experimental or control condition. The randomization schedule will be generated electronically by a researcher not involved in the assessments. Group allocations will be kept in sequentially numbered sealed opaque envelopes. Participants will be informed about the random allocation procedure. Blinding of the investigator will not be possible because the investigator will conduct parts of the assessments and training procedures.

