#### Neuronal efficiency in the sensorimotor brain system

Age-related decline in sensorimotor performance has been linked to decreased neuronal efficiency in the sensorimotor system with respect to reduced motor cortex excitability [62, 63]. To investigate motor cortex excitability at baseline and after the intervention, we will perform single-pulse transcranial magnetic stimulation (TMS) at the left primary motor cortex (M1) and simultaneous recording of motor-evoked potentials (MEP) at the right abductor pollicis brevis. As measures of motor cortex excitability, we will calculate MEP peak-to-peak amplitudes and latencies. Prior to the stimulation, we will determine individual resting motor threshold (RMT), defined as the stimulation intensity at which at least 6 out of 10 MEPs reached a peak-to-peak amplitude of ≥50 μV [64]. We will then conduct three stimulation runs at 100, 110 and 120% of the RMT intensity in pseudorandomized order. Each run will consist of 20 consecutive stimulations with an inter-stimulus interval of approximately 10 s.

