#### BDNF serum level assessment and genotyping

Blood samples collected by the study psychiatrist will be processed according to standard protocols and stored at − 80 °C until analysis. BDNF serum levels as a marker of synaptic plasticity will be measured using a highly sensitive fluorometric enzyme-linked immunoabsorbent assay (ELISA). For genetic analyses, we will extract DNA from blood samples. GWAS analysis will be performed on an Illumina GSA1.0 SharedCustom Content bead array according to the manufacturer’s instructions. GenomeStudio 2.0 software will be used to determine BDNF genotypes and results will be exported in PLINK format.

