### Data analysis and handling

We will use mixed repeated measures analyses of variance for each of the outcome variables in order to assess the effect of the training at baseline, after 60 days, and after 90 days, as well as to unveil differences between the two groups. Significant time-by-group interactions will be further examined using post-hoc tests. To evaluate changes through the interventions, pre-post effect sizes will be computed and compared across interventions. The problem of missing data will be handled using multiple imputation.

Data collected in this project will be recorded, stored and analyzed anonymously. A list assigning codes to names will be stored separately under high security standards. Analysis of the data will be of scientific purpose only.

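### The article declares researchers unblinded without exception, but its reason covers only the investigator who tests and trains, not off-line processing and analysis

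*Protocol article*

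**What the plan says.** The protocol article addresses blinding in two places.

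- **Randomization and blinding (Methods):** "Blinding of the investigator will not be possible because the investigator will conduct parts of the assessments and training procedures". The same section says of the allocation schedule that it is "generated electronically by a researcher not involved in the assessments".
- **Strengths and limitations (Discussion):** "Researchers and participants will not be blinded to treatment condition". The article then relies on random assignment and an appropriate active control to remove expectation effects and systematic bias.

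On data handling, the section Data analysis and handling says: "Data collected in this project will be recorded, stored and analyzed anonymously", and "A list assigning codes to names will be stored separately under high security standards".

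Several outcomes are produced away from the participant. On MEPs the article says: "As measures of motor cortex excitability, we will calculate MEP peak-to-peak amplitudes and latencies". Scans are used for finger maps in the somatosensory cortex and for voxel-based morphometry. Blood is frozen and assayed later. Missing data are multiply imputed, outcomes are analysed by mixed repeated-measures ANOVA, and significant time-by-group interactions are followed by post-hoc tests.

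**The concern.** The limitation is wider than its justification. Someone who trains and tests a participant necessarily knows the arm. Someone who later extracts a cortical map, rejects or scores an MEP trace, or settles an imputation model has no such need.

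These steps involve judgement: which regions and thresholds to use, which traces to discard, what counts as an outlier, what enters the imputation model. If the arm is visible, those judgements can lean towards the hypothesis without anyone intending it. The imaging, stimulation and BDNF measures carry the article's claim to link markers of neuroplasticity with changes in frailty status, and each arm has at most 30 participants, so a few participant-level decisions can matter.

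The named safeguards act elsewhere. Randomisation makes the arms comparable at entry. An active control narrows the difference in participants' expectations. Neither acts on decisions taken after the data have been collected.

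**Working it through.** **1. The plan's own figures.** The article's design figures are not in dispute and masking does not alter them. With f = 0.25, three assessments (m = 3), correlation 0.50 and alpha 0.05, the interaction test has noncentrality f²·N·m/(1 − ρ) = 0.0625 × 44 × 3 / 0.5 = 16.5 at N = 44. The degrees of freedom are 2 and (44 − 2) × 2 = 84. Power is 0.956, against 0.946 at N = 42, which reproduces 22 per group. For 25% drop-out, 22 / 0.75 = 29.3, rounded up to 30 per group.

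**2. Does the stated reason reach each step?** The reason is contact with the participant during testing or training.

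| Step | Article section | Needs contact? | Room for judgement |
|---|---|---|---|
| Grip, gait and other face-to-face tests | Frailty status; Sensorimotor performance | Yes, reason applies | Substantial |
| fMRI map extraction, voxel-based morphometry | Brain plasticity in the sensorimotor and somatosensory system | No | Substantial |
| MEP amplitude and latency scoring | Neuronal efficiency in the sensorimotor brain system | No, scored from recordings | Substantial |
| BDNF assay | BDNF serum level assessment and genotyping | No, stored samples | Small |
| Imputation, ANOVA, post-hoc choices | Data analysis and handling | No | Substantial |

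The reason covers the first row only. The statement under Strengths and limitations excepts none of the others. The last two columns are my reading of the procedures described.

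**3. Are the means of masking at hand?** Partly. Participant codes exist, but the separate list links them to names. They hide identity; the article does not say that they hide the arm. They would mask the arm only if the allocation were also withheld from those who process and analyse the data. A researcher outside the assessments already generates the schedule and could hold that key.

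**4. Can the bias be sized?** Not from the documents. They do not say how many defensible processing choices exist, how strongly their results correlate, or who makes them.

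**The case against.** **This is a condensed article.** Masking of image and laboratory processing, artefact rules and code locking are commonly left to the full protocol or analysis plan, so silence on them would be no finding. That stands. The point here rests on what is stated: an unqualified declaration, defended by safeguards that do not reach these steps.

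**The lack of blinding is disclosed, and the Methods text is narrower.** Both are true. Disclosure does not settle the part that is avoidable, and the narrower Methods reason is exactly why the wider statement needs trimming.

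**A reader might infer that every researcher knows the arm and that processing choices are made with it visible.** The documents do not support this. They say researchers without qualification, but never say who scores MEPs, processes scans, runs the assay or analyses the data, or that these people hold the allocation. Equally, the promise of anonymous analysis cannot be read as arm masking.

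**A reader might try to size the harm by simulation.** Assume 3 to 5 pipelines with test statistics correlated 0.7 to 0.9. The chance that at least one exceeds 1.96 in absolute value is 8% to 11% for three and 10% to 15% for five. That does not measure unblinding. It is the either-direction error of an analyst who keeps the largest absolute statistic, which someone seeing only labels X and Y can also do. The rate of false findings favouring training is half of it, 4.2% to 5.5% for three and 5.1% to 7.4% for five. It is the same when an unmasked analyst keeps the largest statistic in the hoped-for direction. In this model X/Y labels at the analysis stage protect nothing. Protection comes from label-free processing and from locking decisions before groups are compared. The inputs are also assumptions with no basis in the documents.

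**The larger exposure lies elsewhere.** For the primary frailty phenotype, which includes grip strength and gait speed, the main risk is an unblinded investigator conducting parts of the assessments. That stands, and this point does not address it.

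**Conclusion.** The point holds in a limited form. The article declares researchers unblinded without exception, and its only reason does not extend to off-line processing and analysis. The safeguards it names do not protect those steps.

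No numerical size can be given. The case is strongest for imaging, MEP scoring and the analysis choices, and weak for the BDNF assay. It concerns mainly the mechanistic outcomes. For the primary outcome, locked analysis decisions help only at the analysis stage and leave any bias from unblinded testing in place.

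The conclusion assumes that the limitation means what it says and that off-line work is feasible without contact with participants, as the described procedures indicate. If the full protocol already masks these steps, only the wording under Strengths and limitations needs correcting. The change is worth making because it is cheap and reduces an avoidable source of bias.

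**What to change.** **Randomization and blinding.** Add wording to this effect:

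- MRI, MEP and blood data are processed on re-coded files that carry no arm labels.
- Processing decisions, the imputation model and the analysis code are locked before any between-group comparison is run.
- The researcher who generated the schedule holds the arm key until the lock is recorded.

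The order matters: a lock after an X-versus-Y comparison has been seen would not serve. The app training data should stay out of the re-coded files until the lock, because their content differs by arm (achievements in one, post-session affect items in the other).

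**Strengths and limitations.** Confine the statement to participants and the staff who train and test them, and keep unblinded testing of the primary outcome as a declared limitation.

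**Cost.** Protocol wording and one re-coding step by existing staff. No extra assessor, reader or visit is needed, and sample size, power and alpha are unchanged.

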## Data Availability

The datasets produced by the completed study will be available from the corresponding author on reasonable request.

## Abbreviations

AST: Attention Switching Task
BDNF: Brain-derived neurotrophic factor
CANTAB: Cambridge Neuropsychological Test Automated Battery
CES-D: Center for Epidemiologic Studies Depression Scale
CTSIB: Clinical Test of Sensory Integration of Balance
EQ-5D-5L: EuroQol-5D-5L
EPI: Echo-planar imaging
FEFA: Frail Elderly Functional Assessment
FES-I: Falls Efficacy Scale – International Version
FoV: Field of view
IED: Intra-Extra Dimensional Set Shift
M1: Primary motor cortex
MEP: Motor-evoked potential
MKS: Marburg Competency Scale (Marburger Kompetenz Skala)
MMSE: Mini Mental State Examination
MNA: Mini Nutritional Assessment
MRI: Magnetic resonance imaging
PANAS: Positive and Negative Affect Schedule
PPT: Purdue Pegboard Test
RMT: Resting motor threshold
RTI: Reaction Time
S1: Primary somatosensory cortex
SF-36: Short Form-36
SPPB: Short Physical Performance Battery
SSP: Spatial Span
T0: Baseline assessment
T1: Assessment 1
T2: Assessment 2
TE: Echo time
TMS: Transcranial magnetic stimulation
TR: Repetition time
